## Abstract

**Introduction:**

Many people living with advanced dementia live and die in nursing care homes. The quality of life, care and dying experienced by these people is variable. Namaste Care is a multisensory programme of care developed for people with advanced dementia. While there is emerging evidence that Namaste Care may be beneficial for people with dementia, there is a need to conduct a feasibility study to establish the optimum way of delivering this complex intervention and whether benefits can be demonstrated in end-of-life care, for individuals and service delivery. The aim of the study is to ascertain the feasibility of conducting a full trial of the Namaste Care intervention.

**Methods and analysis:**

A feasibility study, comprising a parallel, two-arm, multicentre cluster controlled randomised trial with embedded process and economic evaluation. Nursing care homes (total of eight) who deliver care to those with advanced dementia will be randomly allocated to intervention (delivered at nursing care home level) or control. Three participant groups will be recruited: residents with advanced dementia, informal carers of a participating resident and nursing care home staff. Data will be collected for 6 months. Feasibility objectives concern the recruitment and sampling of nursing homes, residents, informal carers and staff; the selection and timing of primary (quality of dying and quality of life) and secondary clinical outcome measures (person centredness, symptom presence, agitation, quality of life, resource use and costs and residents’ activity monitored using actigraphy). Acceptability, fidelity and sustainability of the intervention will be assessed using semistructured interviews with staff and informal carers.

**Ethics and dissemination:**

This protocol has been approved by NHS Wales Research Ethics Committee 5 (ref: 17/WA0378). Dissemination plans include working with a public involvement panel, through a website (http://www.namastetrial.org.uk), social media, academic and practice conferences and via peer reviewed publications.

**Trial registration number:**

ISRCTN14948133; Pre-results.

Strengths and limitations of this studyIntervention trialled is based on a theoretical model of how the intervention works, drawn from current evidence base and consultation with care home staff, family and experts.Public and Patient Involvement (PPI) will greatly inform the ongoing development of the research design and delivery and assist in recruitment, analysis and dissemination.Both proxy and objective measures will be measured with this hard to research population.Blinding is not possible due to the nature of the intervention.The study will not provide data on the effectiveness of the intervention, but will indicate if a further trial to establish effectiveness is feasible.

## Introduction

### Background

Dementia is a life-limiting condition, with a median survival, decreasing with age, of 6.7–1.9 years.^1^ In advanced dementia, an individual requires full assistance with care is chair or bedbound, doubly incontinent and no longer able to communicate verbally (Functional Assessment of Staging of Alzheimer’s Disease (FAST) scale 6–7).^2^ People with dementia often experience a poor quality of death, preceded by a period of poor quality of life, with over and under treatment occurring.^3–5^ There is an increasing urgency for appropriate care that will ensure a good quality of life and dying are achieved.^5 6^

Evidence for therapeutic healthcare interventions for people with advanced dementia is limited. Reviews of therapies such as music therapy indicate mixed outcomes for people with dementia, with a Cochrane review identifying equivocal evidence.^7^ More recent reviews of therapeutic interventions have identified large positive effects on behavioural, cognitive and physiological outcomes,^8^ to moderate effects on anxiety with small effects on behavioural symptoms and evidence for short-term improvement in mood and reduction in behavioural disturbance.^9 10^ In a Cochrane review of touch therapies, some evidence of an effect was identified, but not specifically for people with advanced dementia.^11^ A recent review indicated that massage reduced levels of agitation.^12^ Interventions supporting person-centred care have been shown to reduce agitation and behavioural disturbance. There is some evidence for individualised interventions, within a bio-psychosocial framework, improving behavioural symptoms.^13–15^

Interventions with a single focus on reducing pain, physical symptoms or specific behavioural disturbances have been found to be effective.^3^ It is recognised that for people with advanced dementia there is a need for interventions that complement and enhance pharmacological interventions. This study addresses the lack of evidence available through completed research, to consider the stage-specific efficacy of non-pharmacological interventions.^16^ There is also a need for practical interventions that staff can learn to deliver which allow them to provide person-centred care.

Palliative and end-of-life care interventions for people with dementia that emphasise a person-centred philosophy, and use co-design approaches, are being developed and tested.^17^ Namaste Care is one such intervention. Non-randomised research studies have identified that Namaste Care at the end of life reduces the severity of behavioural and physical symptoms and occupational disruptiveness and may have an impact on social interaction, delirium and agitation.^18–22^ The potential for cost savings with respect to reduced psychotropic medication use has also been indicated.^19 23^ Qualitative evidence suggests greater family and staff satisfaction with care.^18^ However, none of these studies have compared this intervention with other approaches to palliative and end-of-life care for this population. We do not yet know the optimum way of delivering this complex intervention and which benefits (including cost-effectiveness) can be demonstrated in end-of-life care, for individuals and service delivery.

In Phase i of this study, a realist review of 85 papers that considered Namaste Care and sensory interventions (such as music therapy or massage) for people with advanced dementia identified three context–mechanism–outcome configurations. This indicated what needs to be in place for Namaste Care to work for this population. The overarching theme was the importance of providing activities that enabled the development of moments of connection for people with advanced dementia. This can occur when the following three elements are in place: provision of structured access to stimulation (social and physical), equipping care home staff to be able to cope with complex variable behaviours and providing a framework for person-centred care.

### Intervention development

The Namaste Care intervention is already promoted using existing resources.^24 25^ In this study, a four-stage approach to the development and refinement of the intervention resources was used. This entailed (1) collating the existing intervention materials and the findings of the realist review to draft an intervention description; (2) exploring the readability, comprehensibility and utility of the materials with staff unfamiliar with Namaste Care; (3) using a modified nominal group techniques with people with Namaste Care experience to refine and prioritise the intervention implementation materials; and (4) final refinement with the study’s patient and public involvement panel. This led to production of a 16-page A4 booklet. The booklet included the use of flow charts, graphics and colour-coded information supported by infographics, and a training package.

Therefore, we propose undertaking a feasibility cluster controlled randomised trial in a nursing care home context between 1 January 2018 to 31 March 2019.

### Aims and objectives

The primary objective of this feasibility study is to ascertain the feasibility of conducting a full trial of the Namaste Care intervention.

The feasibility issues associated with the research design and data collection processes to enable the design of a full trial to determine the efficacy of Namaste Care areTo understand how best to sample and recruit nursing homes into a cluster randomised controlled trial of Namaste Care.To determine the most appropriate selection, timing and administration of primary and secondary outcome measures for a full cluster randomised controlled trial of Namaste Care against criteria of bias minimisation, burden and acceptability.To establish recruitment, retention and attrition rates at the level of the nursing home and individual resident, informal carer and nursing home staff.To establish the willingness of a large number of nursing homes representing the range of nursing homes, with respect to provider type, size, resident care needs, to participate in a full trial.To assess the acceptability, fidelity and sustainability of the Namaste Care intervention.

Secondary objectives include resident levels of sleep/activity, neuropsychiatric symptoms and pain, informal carer satisfaction with care at the end-of-life staff care giving experiences and satisfaction with care in end-of-life care. Health economic and healthcare resource use will also be assessed.

## Methods and analysis

### Trial design

A feasibility study consisting of a parallel, two-arm, multicentre cluster controlled randomised trial design with an embedded process evaluation is to be conducted. The clustering will take place at the nursing care home level. The Namaste Care programme in the intervention arm will be compared with the standard programme of care used in the control homes.

### Study population

#### Nursing care homes

Eight nursing care homes based in the northwest of England already using a recognised palliative care programme (eg, Gold Standards Framework for Care Homes, Six Steps to Success or equivalent) will be recruited into the study. Two nursing care homes will be allocated to the control arm while six nursing care homes will be allocated to the intervention arm. To meet the eligibility criteria, the nursing care home needs to haveAt least 30 beds.Six residents who meet the resident eligibility criteria.The space to run the Namaste Care programme.A manager or a nominated person to act as the principal investigator.

A nursing care home will not be eligible to join the study if theyAre rated as needs improvement or inadequate in the latest Care Quality Commission (CQC) inspection.Are subject to (CQC)enforcement notices.Have already introduced Namaste Care in their nursing care home.Are currently involved in another research study that conflicts with this study.

#### Individual participants

Residents: To meet the resident eligibility criteria, a resident has toBe a permanent resident living in the participating nursing care home.Lack mental capacity.Have a formal assessment of advanced dementia based on the FAST score of 6–7 made by the nursing care home manager or another experienced member of staff.Have a key worker member of staff willing to complete outcome tools.

A resident will be ineligible to participate in the study if the residentIs permanently bedbound.Is currently or has recently been involved in another research study that conflicts with Namaste Care or with data collection during the course of the Namaste Care study.

Informal carer: To meet the informal carer eligibility criteria, a person whoIs 18 years and over.Can communicate in English.Self-defines as a relative or a friend and acts a carer for a resident enrolled to take part in the study.

A person will not be eligible to participate in the study ifTheir relative or friend is a resident and has not been enrolled in to the study.

Nursing care home staff: To meet the nursing care home eligibility criteria, a person has to beA member of health and social care staff paid to provide care to residents with advanced dementia within participating nursing care homes.

Nursing care home staff will not be eligible to participate in the study ifThey are in the intervention arm and they have delivered the Namaste Care programme or cared for residents receiving Namaste Care in a nursing care home not involved in this study.

#### Sample size and selection

As the aim of this study is to establish feasibility of a full trial, a formal sample size calculation was not carried out. A sample size of eight nursing homes (six interventions and two controls) has been selected as it offers a reasonable test of the intervention to assess the feasibility objectives. There have been a range in the sample sizes used in feasibility studies in nursing homes ranging from 2^26^6 to 14.^27^

Eligible nursing care homes will be identified through online resources such as the ENRICH database. Following the initial identification, contact will be made with managers of the nursing care home to discuss the study and confirm the eligibility of the nursing care home. Consent for the homes will be assumed when the manager of the facility signs a contract drawn up by the sponsor, Lancaster University.

### Randomisation

The randomisation of participating nursing care homes to either the intervention arm or the control arm will be undertaken by statisticians from the Clinical Trials Research Centre (CTRC) at the University of Liverpool randomisation team who will not be involved in the study. Due to the clustered randomisation approach of this study, all study participants will be assigned to the same study arm as the nursing care home they are associated with. The nature of the intervention and its delivery means that it will not be possible to blind nursing homes or staff to the allocation status. If possible, to minimise potential for bias, staff involved in the delivery of the Namaste Care intervention will not be involved in the completion of outcome measures. It will not be possible to blind researchers to the allocation of nursing homes as the intervention requires changes to the nursing home environment which may be visible to any researcher visiting the facility.

The study flow chart of activities (figure 1) show the recruitment process to be followed.

**Figure 1 F1:**
[figure not shown]
Flow diagram outlining the process of the study.

### Consent procedures

#### Individual participants

Residents: Potentially eligible residents will be screened by the principal investigator and the senior care team at each nursing care home. Consent for the eligible residents will be sought from a personal consultee of the resident in the first instance. If a person consultee does not reply within month of been given the invitation pack, then assent will be taken from either a nominated consultee or the process used by the nursing care home in question. Once permission is granted by the personal consultee, members of the research team will discuss the study with the personal consultee and gain assent for residents to take part in the study. Process consent will also be considered for the resident participant group.^28^ Therefore, if a resident shows signs of not wanting to take part in the Namaste Care session they will be allowed to miss the Namaste Care session and still continue in the trial.

Informal carer: The informal carers of residents enrolled to the study will be identified by the principal investigator and the senior care team at each nursing care home and invited to consent to complete questionnaires and participate in a qualitative interview.

Nursing care home staff: Nursing care home staff interested in taking part in the Namaste Care study will be identified by the nursing care home manager. On identification, researchers will discuss the study with the identified staff members and obtain written consent from each staff member.

A research lead will be appointed in each nursing care home. The research lead will be tasked with ensuring the paperwork associated with clinical research and the Investigator Site File is maintained. The research lead and the principal investigator from the intervention sites and the control sites will be invited to a training day for guidance on selection of participants and completion of data collection forms and maintaining the Investigator Site File.

Participants will be followed for 6 months after the commencement of the Namaste Care intervention in each nursing care home in the intervention arm or after the recruitment of the first four residents in the nursing care home for sites in the control arm.

### Intervention

The intervention is a programme of care (Namaste Care), delivered in the intervention care homes by care staff working in the facility. The following description uses the TIDieR guidelines for intervention description (items 1–9).^29^

Namaste Care seeks to give comfort and pleasure to people with advanced dementia through engagement, meaningful and creative activities as well as sensory stimulation to reflect the resident’s ‘life story’.^24^ Supporting resource materials have been developed which provide the following guidance regarding the implementation of Namaste Care programme.The Namaste Care sessions should be undertaken within a designated space in the nursing home. This space could be within another room or a room which is used for other purposes.The environment of the designated space must be made ‘special’ and should enable a feeling of calm that is welcoming and homely, with natural or slightly dimmed lighting, perhaps attractive scents, such as lavender from an aromatherapy diffuser, and with soft music playing.The Namaste Care sessions should be undertaken in a group setting.Food and drink should be offered to the residents.A minimum of two nursing home staff members or volunteers should be present to run the Namaste Care sessions.The duration and frequency of Namaste Care delivery as proposed by its originator (2 hours a day, twice a day, 7 days a week) will be promoted.^24^

Namaste Care champions will be appointed in each nursing care home in the intervention arm. At least two care staff (registered nurses, care assistants or activity coordinators) will attend a 1-day workshop about Namaste Care, led by an experienced external facilitator. A follow-up training session will be held at each nursing care home to train more staff and provide advice on preparing the Namaste space.

Prior to the commencement of enrolment, Namaste Care champions (eligible nursing care homes will be identified in the intervention arm) will be appointed in each nursing care home. The Namaste Care champion will be invited to a training day for guidance on Namaste Care intervention, held at a site away from nursing care homes and undertaken by members of the research team and an external trainer. A follow-up training session will be held at each nursing care home.

### Control arm

The care home manager of nursing care homes allocated to the control arm will be asked to continue delivering the usual care programme used in their facility.

Training on the Namaste Care programme will be available to the nursing care homes in the control arm after the study has been completed.

### Outcome and study measures

We consider two contender primary outcomes for a full trial: (1) quality of dying (dementia) (CAD-EOLD) and (2) quality of life (QUALID) (tables 1-4).^30 31^

**Table 1 T1:** Summary of resident data collected by care home staff, outcome measures and time schedule

Data collected and tool used		Pre-intervention	Monthly	At 6 months or death	
Socio-demographics	Age, gender, ethnicity, existing medical conditions, stage of dementia on Functional Assessment of Staging of Alzheimer’s Disease score	x	x	x	
Quality of dying	Measure to assess quality of death using CAD-EOLD (Comfort Assessment in Dying with Dementia)^47 48^	x	x	x	
Quality of life of the person with dementia	EQ-5D-5L^38^ self-rated health index and visual analogue scale of current health state	x	x	x	
Neuropsychiatric Inventory (Neuropsychiatric Inventory–Questionnaire)	Measure to assess psychiatric state of resident using NPI-Q^39^	x	x	x	
Pain	Measure to assess level of pain using PAIN-AD^35^	x	x	x	
Quality of life	EQ-5D-5L	x	x	x	
ICECAP Supportive Care Measure	Health economic measure using ICEPCAP-SCM^39^	x	x	x	
ICECAP-O measure (CEpop CAPability measure for Older people)	Health economic measure using ICEPCAP-O^49^	x	x	x	–
Cohen-Mansfield Agitation Inventory	Measure to assess resident agitation^36^	x	x	x	
ICECAP Supportive Care Measure using Think Aloud	Health economic measure using ICEPCAP-SCM using Think Aloud	x	x	x	
ICECAP-O measure using Think Aloud	Health economic measure using ICECAP-O using Think Aloud	x	x	x	

**Table 2 T2:** Summary of informal carer data collected, as assessed by informal carers, outcome measures and time schedule

Data collected and tool used		Baseline	At 1 month	At 6 months or death
Socio-demographics	Age, gender, ethnicity, existing medical conditions	x	–	–
Service use in the prior month	Client Service Receipt Inventory^50^ Calculates service and total care costs	x	x	x
Quality of life of the carer	EQ-5D-5L	x	x	x
Satisfaction with care	SWC-EOLD (Satisfaction with Care at the End-of-Life in Dementia)^34^	x	x	x
ICECAP Close Person Measure of health economic evaluation	Health economic evaluation using ICECAP-CPM	x	x	x
ICECAP Close Person Measure of health economic evaluation	Health economic evaluation using ICEPCAP-CPM completing using Think Aloud	x	x	x

**Table 3 T3:** Summary of staff data collected as assessed by care home staff: outcome measures and time schedule

Data collected and tool used		Preintervention	6 months
Staff socio-demographics	Age, gender, ethnicity	X	–
Staff work characteristics	Highest qualification, role in care home, length of service	X	–
Organisational support for person-centred care	The Person-Centred Care Assessment Tool 32	X	X
Organisational support for readiness for change	The Alberta Context Tool Questionnaire^51^	X	–

**Table 4 T4:** Summary of nursing care home level data collected, outcome measures, time schedule and the type of person assessing the outcome measure

Data collected and tool used		Pre intervention	Monthly	At 6 months only	Postintervention
Care home occupancy level	Number of available beds to new residents	S	–	–	–
Cost of living in the care home	Fees to live in the care home	S	–	–	–
Contributions from local government	Fees paid by the local government for each resident	S	–	–	–
Staffing levels	Number and type of staff	S	–	–	–
Number of GP practices the care home works with	Number of GP practices the care home works with	S	–	–	–
Number of GPs the care home works with	Number of GPs the care home works with	S	–	–	–
Level of need of residents in the care home	Amount of support each resident needs	S	–	–	–
Staff turnover and sickness levels	Number of staff in the care home and monthly sickness record	S	S	–	–
Ambulances and hospital use	Number and length of hospital admissions (days), A&E attendances and readmissions	S	S	S	–
Number of hospital admissions	Respiratory infections, urinary tract infections, dehydration, congestive heart failure?	S	S	S	–
Out of hours GP contacts	GP visits or telephone contact	R	R	R	R

Measure assessed by S: care home staff; R: researcher.

The secondary outcome measures in this trial (table 1) will measure measure person centredness, symptom presence, agitation, quality of life, resource use and costs; and sleep and activity using actigraphy.^32–37^Semistructured interviews with staff and informal carers will assess perceptions of Namaste Care or usual care, assessment of the fidelity, acceptability and appropriateness of Namaste Care or of usual care.

The outcome measures to be used are listed in tables 1–4 and presented based on respondent type, that is, measures for residents (table 1), informal carers (table 2), staff (table 3) and at the level of the nursing care home (table 4). At the start of the study, descriptive data will be collected for all participating nursing care homes such as ownership and funding model, size, staffing, case mix, staff turnover, staff sickness/absence and geographical location. An interview with the nursing care home manager will also be conducted to ascertain the organisation’s readiness for change.

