### Data collection

In this study, the outcome measures and process evaluation data will be gathered via five different methods:Questionnaires: The nursing home staff participant group and the informal carer participant group will be asked to complete written questionnaires at timepoints outlined in tables 1–3. The questionnaires for the resident participant group will be proxy completed by nursing care home staff who are key workers for the participating residents. Note the time frame for baseline varies depending on the participant group. Data on nursing home level data about engagement with health and social care services will be collected using standardised data collection forms (table 4).Objective measures: The participating residents will be asked to wear an actigraph watch-like device for 28 days from the baseline visit. This actigraph will be placed on the wrist or ankle of the resident and will be used to continuously measure sleep and activity.Interviews: Semi structured interviews will be undertaken at the baseline with the nursing home manager and at the end of the data collection period with family carers and care staff.Observations of the residents will be undertaken intermittently during the delivery of the care programme and during the delivery of usual care in the control sites.Data logs will be completed in the intervention sites using a proforma to record intervention delivery.

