#### Feasibility work for economic evaluation

The use of a number of potential outcome measures will be explored in terms of feasibility and acceptability of proxy completion with the particular population, evaluated through the Think Aloud technique. The chosen measures are included in the National Institute for Health and Care Excellence-recommended measures for health and social care: EQ-5D-5L (five items), the ICECAP-O (five items) and the ICECAP-Supportive Care Measure (ICECAP-SCM) (seven items).^38–40^ A Think Aloud technique will also be used with the ICECAP-O, ICECAP-SCM and ICECAP-CPM tools for a proportion of participants at 2, 4 and 24 weeks, to obtain 20–30 Think Aloud interviews across a range of timepoints.^41^ This Think Aloud technique will be undertaken either via telephone or face to face. The feasibility of collecting resource use data through nursing home records will be assessed, and the cost of the interventions will be estimated, for use in a full evaluation.

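### QUALID is named as one of two contender primary outcomes, but no table and no text in the protocol article schedules its collection

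*Protocol article*

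**What the plan says.** All references are to the protocol article.

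- **Outcome and study measures** opens with the two candidates: "We consider two contender primary outcomes for a full trial: (1) quality of dying (dementia) (CAD-EOLD) and (2) quality of life (QUALID". The sentence refers the reader to Tables 1–4.
- **The same section** later gives those tables their status: "The outcome measures to be used are listed in tables 1–4 and presented based on respondent type".
- **Data collection** takes the timing from the tables too. Staff and carers are to "complete written questionnaires at timepoints outlined in tables 1–3". For residents the respondent is fixed: "The questionnaires for the resident participant group will be proxy completed by nursing care home staff who are key workers for the participating residents".
- **Table 1** (resident measures) has a row for the first contender, described as "Measure to assess quality of death using CAD-EOLD (Comfort Assessment in Dying with Dementia" and marked pre-intervention, monthly, and at six months or death. Two further rows concern the resident's quality of life. Both name EQ-5D-5L, and both carry the same three timepoint marks. The first describes the instrument as a "self-rated health index and visual analogue scale of current health state".
- **Aims and objectives** makes the choice of outcome a purpose of the study: "To determine the most appropriate selection, timing and administration of primary and secondary outcome measures".

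**The concern.** A feasibility study with two candidate primary outcomes has to collect both. The Quantitative analysis section says what the decision on a full trial will draw on: completion and response rates, missing data, standard deviations, proxy agreement and the intracluster correlation coefficient. Each of these needs completed forms for the instrument concerned.

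As printed, one contender has a full schedule and the other has none. The missing contender is the dementia quality-of-life measure, and the place where one would expect it holds a second entry for EQ-5D-5L. If site staff or form designers work from Table 1, QUALID may never be administered. The loss would be permanent for residents who die during follow-up, and the Monitoring and trial management section describes the risk of death in this population as relatively high.

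**Working it through.** No formula applies, and the article gives no figure to reproduce: it states that no formal sample size calculation was done. The check is a comparison of text with tables.

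**Step 1. Look for QUALID in every table row.**

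| Table | Content | Rows | QUALID rows |
|---|---|---|---|
| 1 | Resident measures | 11 | 0 |
| 2 | Informal carer measures | 6 | 0 |
| 3 | Staff measures | 4 | 0 |
| 4 | Home-level data | 11 | 0 |
| 5 | Process evaluation | 4 | 0 |

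Total: 11 + 6 + 4 + 11 + 4 = 36 rows, none of which names QUALID.

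**Step 2. Look for QUALID in the text.** It occurs once, in the sentence that names the contenders. That sentence gives no respondent and no timepoint. The abstract speaks only of quality of life, without naming an instrument.

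**Step 3. Compare the quality-related rows of Table 1.**

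| Row | Instrument printed | Pre-intervention | Monthly | 6 months or death |
|---|---|---|---|---|
| Quality of dying | CAD-EOLD | x | x | x |
| First quality-of-life row (directly below CAD-EOLD) | EQ-5D-5L | x | x | x |
| Second quality-of-life row (below pain) | EQ-5D-5L | x | x | x |

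**Step 4. Could EQ-5D-5L be standing in for QUALID?** No. The section on feasibility work for the economic evaluation lists the economic candidates as "EQ-5D-5L (five items), the ICECAP-O (five items) and the ICECAP-Supportive Care Measure (ICECAP-SCM) (seven items"), and QUALID is not among them. The literature references differ as well: the contenders sentence cites 30 and 31, whereas the first EQ-5D-5L row cites 38.

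**Step 5. What do two rows suggest?** The abstract lists quality of life twice, once as a primary and once as a secondary outcome. Two resident quality-of-life rows in Table 1 fit that structure, if one was meant for the contender primary and one for the secondary measure. The first sits next to CAD-EOLD, so it is the more plausible place for QUALID. This is an inference, and the article does not say so.

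**Step 6. What would each contender yield under the printed schedule?**

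| Needed for the decision | CAD-EOLD | QUALID |
|---|---|---|
| Scheduled assessments | Yes | None |
| Completion and missing data | Estimable | Not estimable |
| Standard deviation | Estimable | Not estimable |
| Intracluster correlation | Estimable | Not estimable |
| Information on timing | Yes | None |

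**Step 7. The self-rated label.** Residents must lack mental capacity to be eligible, Table 1 is headed as collected by care home staff, and Data collection has resident questionnaires completed by proxy. Describing the resident EQ-5D-5L as self-rated conflicts with this. It is a loose descriptor, since the operating rule is clear elsewhere.

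**The case against.** The strongest reply is that this is a table-entry slip in a condensed article. The tables are titled as summaries, and the ethics-approved protocol and the case report forms are not shown. Those may well contain QUALID. The duplicate EQ-5D-5L row supports this reading. It stands as a limit: the article cannot show that QUALID went uncollected, only that it is not scheduled here. It does not remove the point, because the article itself says the measures to be used are in Tables 1–4. A named contender that is absent from them is a contradiction within the document, and not a detail left to a fuller one.

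A second reply is that the tables are visibly incomplete. Actigraphy is attributed to Table 1 and has no row there. That is true, but actigraphy is scheduled in the text under Data collection, for 28 days from the baseline visit. QUALID has neither a row nor such a sentence.

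Three stronger readings are tempting, and the document supports none of them.

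- **A count of lost or duplicated forms.** A reader might multiply eight homes by six residents and by the number of visits. Six is the number of eligible residents a home needs to enter the study, not an enrolment figure, and control-home follow-up starts after the first four residents are recruited. No enrolment target is stated, so such a count has no basis.
- **EQ-5D-5L is administered twice per visit.** A repeated table line does not establish that.
- **CAD-EOLD becomes the primary outcome by default.** No such rule exists. The stated criteria for choosing measures are bias minimisation, burden and acceptability.

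**Conclusion.** The point holds as an internal inconsistency between the statement of contender outcomes and the data-collection schedule. One of the two contenders has no scheduled assessment: 0 of 36 table rows and no sentence of text. Under the printed schedule, the objective on selecting and timing the primary outcome cannot be met for QUALID.

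Confidence is high that the discrepancy exists. The consequence is conditional, since it assumes that collection follows the article's tables. If the full protocol and forms already include QUALID, the damage is confined to the published schedule. It should be corrected in either case, because it touches a candidate primary outcome and is cheap to put right. The self-rated wording is minor.

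**What to change.** 1. Confirm from the full protocol and the case report forms whether QUALID is collected, by whom and when.
2. If it is, or is to be, correct Table 1 so that one of the two EQ-5D-5L rows reads QUALID, most plausibly the first, next to CAD-EOLD. State that the key worker completes it by proxy, at timepoints that allow comparison with CAD-EOLD, and check that the forms agree.
3. If QUALID is not to be collected, amend the statement of contender primary outcomes instead.
4. Reword the description of the resident EQ-5D-5L so that it agrees with proxy completion.

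**Cost.** This is one table row and a check of the forms. If EQ-5D-5L really is completed twice, replacing one copy leaves the number of instruments unchanged. If it is not, and QUALID is not already on the forms, key workers take on one more proxy instrument at each visit where it is scheduled. Burden is one of the study's own criteria for choosing measures, so that addition should be weighed openly.
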